Despite the significant anti-hypertensive effects demonstrated in the FlaxPAD trial, the results contained some important limitations. Firstly, participants of the FlaxPAD trial were already on anti-hypertensive medication yet still exhibited poorly controlled blood pressure [8]. Therefore it is not possible to conclude if flaxseed can reduce blood pressure as a monotherapy or if it is only effective in conjunction with anti-hypertensive medication. Secondly, it remained unclear if flaxseed could effectively reduce blood pressure in hypertensive patients without coexisting peripheral arterial disease. Therefore, despite evidence showing the potential of flaxseed as a potent cardioprotective functional food, the efficacy of flaxseed as an independent treatment to reduce blood pressure in newly diagnosed patients with primary hypertension has yet to be investigated.

The hypothesis to be tested in the present study is: dietary flaxseed will reduce blood pressure in patients with newly diagnosed hypertension and will reduce the need for anti-hypertensive medication. In order to test these hypotheses, a phase II, randomized, double-blinded, controlled clinical trial called HYPERFlax has been designed. The acronym for the HYPERFlax trial stands for the anti-HYPERtensive effects of dietary Flaxseed. Parameters such as blood pressure, plasma and urine metabolomics, plasma lipid profiling, and plasma vascular tone regulators will be analyzed to assess the efficacy and mechanisms of action of dietary flaxseed in hypertension management.

The aims of the HYPERFlax trial are to:

1. determine if consuming 30 g of milled flaxseed daily can effectively reduce blood pressure over six months in newly diagnosed stage 1 primary hypertensive participants;

2. determine if dietary flaxseed is efficacious as a monotherapy;

3. determine if flaxseed can reduce the need for anti-hypertensive medication; and

4. identify the mechanisms of action responsible for the potential anti-hypertensive effects of flaxseed.

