The secondary outcome measures also include anthropometrics, food intake, and physical activity. At baseline, the participants will be asked to fast (9 to 12 hour overnight fast) for blood and urine collection. The blood and urine will be analyzed utilizing techniques including metabolomics and lipid profiling. Biological specimens will be coded with an anonymous patient code and locked in a -80°C freezer. Height, weight, and waist circumference will be measured and body mass index (BMI) will be calculated to assess if the intervention may cause any changes in weight or waist circumference. They will also be asked to fill out a 24-hour food recall form with the study coordinator using the multiple-pass method as established by the United States Department of Agriculture [13] and the standardized international physical activity questionnaire (short) [14]. These two surveys are used to assess the participants’ typical food intake and physical activity habits. These assessments will be repeated at two, four, and six months to assess any changes in diet or physical activity over time, as detailed in Figure 1.

#### **
*Biochemical analysis*
**

The secondary analysis will include the biochemical analysis of plasma or blood. Biochemical analysis also will be performed to determine potential anti-hypertensive mechanisms of action and adherence to intervention. Plasma samples from baseline, two, four, and six months will be analyzed for lipid profiles, metabolomics profile, and for any circulating plasma component that may influence blood pressure regulation. Plasma analysis of alpha-linolenic acid and enterolignans will act as adherence markers. Urine samples from baseline, two, four, and six months will also be analyzed for metabolomics profiling.

#### **
*Statistical analysis*
**

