All data will be stored without identifiable participant information in a password protected electronic document or locked cabinet. The final trial data set will be accessible only to researchers involved in the trial and any medical review board that requires access for safety purposes. In the likelihood of an unbalanced data set, absolute values will be analyzed with a mixed two-way repeated measures model with group and time as the between and within factor, respectively. A *post-hoc* comparison of the least squared means with a Tukey’s adjustment will be utilized to determine where the specific differences lie. Absolute change will also be calculated only for participants who provide clinical information and samples at all time points. Absolute change can be analyzed with one way analysis of variance (ANOVA) and the Kruskal-Wallis test, or multiple *t*-tests and the Mann Whitney U test with a false discovery rate correction. Multiple regression may be used to determine the influence of flaxseed on blood pressure while including factors such as age, BMI, gender, diet, or physical activity. Correlations will be utilized to determine relationships between biochemical markers and blood pressure. Subgroup analyses may also be performed, for example, the dichotomization of change in biochemical markers and observing subsequent change in blood pressure. All statistical tests will be set at a significance level of 0.05. Data will be published in peer-reviewed journals and discussed in public forums such as radio and television broadcasts.

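### The correlations of biochemical markers with blood pressure have no named multiplicity correction, so nominally significant relationships are likely by chance if the open-ended panel is large

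*Protocol article*

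**What the plan says.** The fourth aim in the Background is to "identify the mechanisms of action responsible for the potential anti-hypertensive effects of flaxseed". The Biochemical analysis paragraph under Participant assessments links the laboratory work to that aim: "Biochemical analysis also will be performed to determine potential anti-hypertensive mechanisms of action and adherence to intervention". Plasma from baseline and from two, four and six months is to be examined for "lipid profiles, metabolomics profile, and for any circulating plasma component that may influence blood pressure regulation", and urine from the same four visits for metabolomics. Neither a list nor a count of markers is given.

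The Statistical analysis paragraph names the method for relating markers to blood pressure: "Correlations will be utilized to determine relationships between biochemical markers and blood pressure". It gives one threshold: "All statistical tests will be set at a significance level of 0.05". Two multiplicity corrections appear in the same paragraph. One belongs to the mixed model, where a post-hoc "comparison of the least squared means with a Tukey’s adjustment will be utilized". The other belongs to one of the alternatives for absolute change, namely multiple t-tests and "the Mann Whitney U test with a false discovery rate correction". Neither is attached to the correlations, and the correlations are not labelled exploratory.

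**The concern.** Screening many markers against an outcome, each at 0.05, produces significant results in proportion to the number of markers, whether or not any of them matters. The paragraph recognises multiplicity for two other analyses and names a suitable tool, but leaves the correlations with the general 0.05 only. An analyst who follows the text as it stands would report every correlation with p < 0.05 as a relationship. Because the panel serves a numbered aim, chance findings could then be put forward as candidate mechanisms with nothing to separate them from real ones.

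The primary blood pressure comparison, the sample size and the care of participants are not affected.

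**Working it through.** **Plan's own figure.** The article states no error rate for the correlations, so there is none to reproduce. Its power statement concerns differences between groups and across time and has no bearing here.

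**Inputs**
- Level per test: 0.05 (Statistical analysis); two-sided is assumed, as the side is not stated.
- Participants: 100 enrolled with 20% attrition (Settings and participants), so 100 × 0.80 = 80 completers.
- Number of markers m: not stated. Values of 20, 50, 100 and 200 are assumed to show the range.
- Correlation between markers: not stated, so several patterns were tried.
- Scope: one blood pressure measure at one visit.

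**Step 1: size of correlation needed.** With n = 80 there are 78 degrees of freedom. The critical value is r = t/√(78 + t²), with t the two-sided 5% point. This gives |r| of about 0.22, so a weak chance correlation suffices.

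**Step 2: independent markers.** If no marker is related to blood pressure, P(at least one p < 0.05) = 1 − 0.95^m, and the expected number of false findings is 0.05 × m. The expectation also holds when markers are correlated.

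**Step 3: correlated markers.** Null markers were simulated against an unrelated blood pressure variable, with 80 participants and 2,000 runs per setting. The patterns were blocks of 10 with correlation 0.5 or 0.8, and all markers equally correlated at 0.3 or 0.5. The independent case was also simulated and agreed with the formula (0.62, 0.92, 0.99 and 1.00).

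| m | Independent (formula) | Blocks, 0.5 | Blocks, 0.8 | All, 0.3 | All, 0.5 | Expected false findings |
|---|---|---|---|---|---|---|
| 20 | 0.64 | 0.49 | 0.33 | 0.54 | 0.44 | 1 |
| 50 | 0.92 | 0.82 | 0.63 | 0.80 | 0.61 | 2.5 |
| 100 | 0.99 | 0.97 | 0.84 | 0.94 | 0.78 | 5 |
| 200 | >0.99 | >0.99 | 0.98 | 0.99 | 0.89 | 10 |

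**Step 4: when a chance finding is close to certain.** Solving 1 − 0.95^m ≥ 0.95 gives m = 59, and ≥ 0.99 gives m = 90. Both count effectively independent tests.

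**Step 5: with a false discovery rate correction.** Benjamini-Hochberg at 5% across the m markers, in the same simulations, gave at least one rejection in 0.03 to 0.06 of null trials. This applies to a single family with one blood pressure variable.

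**Not counted.** Testing systolic and diastolic pressure, or more than one visit, adds tests. These are correlated within a person, so they cannot be treated as independent and the increase was not quantified.

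**The case against.** The strongest reply is that a journal article condenses the full protocol, and that error control for a secondary biomarker screen can be left to an analysis plan that is not shown. The 0.05 sentence also governs the Tukey-adjusted and false-discovery-rate-corrected tests, so it does not itself declare the correlations uncorrected. This stands in part: the text is silent on adjusting the correlations and does not rule it out. But the paragraph does take up multiplicity. It allots corrections to particular analyses, gives this one none, and closes with a general threshold. An analysis plan that followed it would carry the gap forward.

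Four further objections limit the point, and each has force.
- **No decision rule for mechanisms.** Nothing in the article says that one correlation with p < 0.05 identifies a mechanism. The statistical text speaks of relationships, and the biochemical work is called secondary and refers to potential mechanisms.
- **The correction on absolute change may reach these markers.** That analysis is limited to participants with samples at all time points, so it may include between-group comparisons of the markers. A flaxseed mechanism would be expected to show a group difference as well as a correlation. However, the correction is tied to only one of two alternative methods, and it does not extend to the correlations.
- **The marker count is assumed.** With 20 markers the chance is 0.33 to 0.64, which is far from certain.
- **Visits are not independent tests.** Repeated samples from the same people raise the error by less than their number suggests.

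**Conclusion.** The point stands as a weakness in how a secondary analysis is specified. With the correlations tested at 0.05 and no correction named for them, nominally significant relationships are likely by chance for panels of the kind described: about 0.33 to 0.64 for 20 markers, 0.61 to 0.92 for 50 and 0.78 to 0.99 for 100. Even the lowest of these is more than six times the nominal 5% (0.33/0.05 = 6.6). The figures assume that no marker is related to blood pressure, that there are 80 completers, and that one blood pressure measure is tested at one visit. The panel sizes are illustrative.

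A reader might infer that a false mechanism is almost sure to be found, or that aim 4 would be answered positively whatever the data show. The documents do not support either. Near-certainty needs roughly 60 to 90 effectively independent tests, a count that the article does not give, and it fails for small or strongly inter-correlated panels. Nor does the article make one significant correlation the criterion for a mechanism. What the text supports is a high chance of false marker relationships, with no stated means of telling them from real ones.

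**What to change.** In the Statistical analysis paragraph, state that the false discovery rate correction already in the plan (Benjamini-Hochberg, 5%) also applies to the correlations between markers and blood pressure. Treat them as one family covering all markers, both blood pressure measures and all visits tested. State that correlations passing only the uncorrected 0.05 will be reported as hypothesis-generating and not as identified mechanisms. The simulated 0.03 to 0.06 supports the method for one blood pressure variable at one visit; it was not calculated for the full family or for separate families by sample type.

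Alpha-linolenic acid and the enterolignans should not be made confirmatory mechanism tests on pooled correlations. The Background reports that the earlier trial linked both to blood pressure, so they may be tested separately as pre-specified associations. The report should then note that the Biochemical analysis paragraph also uses them as adherence markers. They track allocation, so a correlation pooled over both groups partly restates the treatment effect.

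The change takes one or two sentences and no new data. The downside is somewhat less power for individual exploratory markers.

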### Settings and participants

The trial will take place at the Health Sciences Centre Hospital and St Boniface Hospital in Winnipeg (Manitoba, Canada). The aim is to enroll 100 participants. Based on the previous FlaxPAD trial [8] the expected attrition rate is 20%, which still allows for a power of 0.80 to detect differences between groups and across time, out of an effect size of 0.7 (SD) at an α level of 0.05. Participants will be recruited through doctor referral or in response to public advertisements and public screening booths. The inclusion and exclusion criteria below fit the criteria of individuals who are not recommended to be administered anti-hypertensive medication immediately according to the Canadian Hypertension Education Program Guidelines [9]. These individuals do not have a systolic or diastolic blood pressure of more than 160/100 mmHg and do not have diabetes or macrovascular target organ damage. The exclusion criteria, therefore, allow a period of time for lifestyle intervention, including new therapeutic strategies like dietary flaxseed, in low-risk hypertensive individuals.

Inclusion criteria includes:

1. stage 1 essential hypertension (average automated systolic blood pressure of 135 to 160 mmHg or diastolic blood pressure of 85 to 100 mmHg) [9];

2. Newly diagnosed; defined as being clinically diagnosed within the last six months. This includes being diagnosed at the screening examination;

3. Male or female;

4. Untreated by medications for hypertension;

5. 18 to 85-years-old and able to provide informed consent;

6. Females who are not pregnant and not planning on becoming pregnant during the course of the trial. A pregnancy test will not be administered for the trial;

7. Subjects who are receiving anti-platelet therapy must be on a stable dose for three months prior to the study;

8. Subjects who are receiving lipid-lowering drugs must be on a stable dose for three months prior to the study;

9. Subjects must have access to freezer space in their residence to hold up to one month of the frozen food products associated with this study.

Exclusion criteria includes:

1. Patients with ischemic pain at rest in limbs, ulceration, or gangrene.

2. Patient has undergone percutaneous coronary angioplasty, or has had coronary bypass within the last six months.

3. Known secondary hypertension of any etiology.

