### Randomization and interventions

Upon acceptance into the trial all participants will be provided information on lifestyle management of hypertension. These strategies include the dietary approaches to stop hypertension, limiting alcohol and salt intake, limiting or stopping cigarette smoking, increasing physical activity, and losing weight if the individual is overweight or obese. However, it is not mandatory to adopt these lifestyle changes to be eligible for the trial.

Immediately after the baseline assessments, subjects will be randomized to one of two possible groups by a non-restricted computer-generated randomization schedule. The allocation ratio will be 1:1. The study coordinator will enroll the participants and the individual in charge of food delivery will be in charge of participant allocation. The allocation order will be in sequential, opaque, sealed envelopes. At this point all those involved in the study will be blinded to the group allocation excluding the individual responsible for food delivery.

The participants will be provided either the control or flaxseed-containing food products such as muffins, bagels, snack bars, and milled seeds to consume once a day for six months. A variety of flavors will be provided to assure the participants do not tire of the foods. In addition, participants will be encouraged to remain in the study and be adherent by describing to them the importance of their contribution to identifying new treatment strategies for hypertension. The control food products will contain a combination of wheat, pecans, and/or mixed dietary oils to replace the flaxseed. This combination of ingredients for the control food product will and has allowed for the best concealment and ability for a blinded trial. The formulation and flavor profiling of the flaxseed food products has been previously published [10,11].

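### The example subgroup analysis splits patients on marker change after randomisation; it discards information and, if arm is ignored, can show allocation rather than mechanism

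*Protocol article*

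**What the plan says.** All of the analysis text is in the Statistical analysis paragraph of the protocol article. The main analysis is a mixed repeated-measures model with group and time, with no covariate measured after randomisation. Three further analyses follow.

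- Correlations, worded as planned: "Correlations will be utilized to determine relationships between biochemical markers and blood pressure". The text does not say whether the arms are pooled, treated separately or adjusted for.
- A multiple regression for the influence of flaxseed on blood pressure, worded as optional, "including factors such as age, BMI, gender, diet, or physical activity". The text does not say at which visit BMI, diet and activity are taken.
- Subgroup analyses, also optional, with the example "the dichotomization of change in biochemical markers and observing subsequent change in blood pressure". No cut-point is given, and the text does not say whether the split runs across both arms.

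Three other places bear on these. Biochemical analysis uses plasma alpha-linolenic acid and enterolignans as markers of adherence, so the plan expects the assigned food to move them. Anthropometrics and questionnaires lists body measures, food intake and activity as secondary outcomes, asks whether the intervention changes weight or waist, and says "These assessments will be repeated at two, four, and six months". The fourth aim, in Background, is to identify how flaxseed lowers blood pressure.

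**The concern.** Change in a marker from baseline is by definition observed after allocation and may be a result of it. Patients sorted by that change are not comparable in the way that randomised groups, or subgroups defined at baseline, are. A difference in blood pressure between them can come from allocation, adherence, other patient characteristics or a real pathway, and the split cannot tell these apart. Cutting a continuous variable in two also discards information.

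For a marker that the food itself raises, a split across all patients tends to put flaxseed patients in the high group and controls in the low group. It then partly repeats the randomised comparison under another name. A correlation that ignores arm has the same weakness. At stake is the mechanism aim: an arm difference could be read as evidence for a pathway.

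**Working it through.** **Inputs from the article.** "The aim is to enroll 100 participants"; "The allocation ratio will be 1:1"; expected attrition of 20%. This gives 100 × 0.8 = 80 completers, 40 per arm. The design effect is 0.7 SD at α 0.05; I take it as two-sided and as a within-arm SD, since neither is stated.

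**The plan's own figure.** Settings and participants claims 80% power for that effect after attrition. With 40 per arm, 0.7 × √(40/2) = 3.130 and 3.130 − 1.960 = 1.170, so power is Φ(1.170) = 0.88 (0.87 with the t distribution). The stated 0.80 is therefore not reproduced exactly, but it is conservative: 33 per arm would be enough, or 66/0.8 = 82.5, rounded up to 83 enrolled. This does not decide the point; only the 80 completers and the 0.7 SD are carried forward.

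**Step 1: information lost by splitting.** Splitting a normal variable at its median multiplies its correlation with another variable by √(2/π) = 0.798. The information kept is 2/π = 0.637, and 80 × 0.637 = 50.9, or about 51 patients. Simulated power with 80 patients (8,000 replicates) was:

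| True correlation | Continuous marker | Median split |
|---|---|---|
| 0.20 | 0.43 | 0.29 |
| 0.30 | 0.78 | 0.57 |
| 0.40 | 0.96 | 0.84 |

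**Step 2: association produced by allocation alone.** Let flaxseed shift a marker by d and blood pressure by e = −0.7, with within-arm SDs of 1, equal arms and no association within arms. Over all patients:

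- covariance = d × e / 4
- marker variance = 1 + d²/4
- blood pressure variance = 1 + 0.49/4 = 1.1225

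For d = 2, the covariance is −0.35 and the marker variance is 2, so r = −0.35/√(2 × 1.1225) = −0.234. With 80 patients, t = −2.12 on 78 degrees of freedom, p = 0.037. The article gives no value for d, so a range is needed. The last three columns are percentages of simulated trials significant at 0.05 (8,000 replicates, 40 per arm):

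| Assumed d (SD) | r by formula | Correlation ignoring arm | Median split ignoring arm | Correlation allowing for arm |
|---|---|---|---|---|
| 0.5 | −0.08 | 10% | 8% | 5% |
| 1 | −0.15 | 25% | 20% | 5% |
| 1.5 | −0.20 | 43% | 36% | 5% |
| 2 | −0.23 | 57% | 53% | 5% |

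The association over all patients is real in a numerical sense, but here it carries no information on mechanism. Allowing for arm removes it.

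**Step 3: why covariate timing needs a sentence.** Suppose follow-up values were used and the covariate carried half of a 0.7 SD effect. In simulation (4,000 replicates) the adjusted estimate falls from 0.70 to 0.35 SD, and power from 0.87 to 0.40. With baseline values this cannot happen, since they precede allocation.

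**The case against.** The strongest reply is that the article commits to little here. The subgroup analysis is optional and given as an example, the regression is optional too, and the main model is sound. That stands, and it limits the importance of the point. It does not remove it: the one subgroup analysis that the article names is a poor one, and a fuller plan would have to reverse that sentence, not merely add detail.

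Two stronger readings are tempting, and the text supports neither.

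- A reader might infer that the correlations pool the arms. The article does not say so; within-arm or arm-adjusted correlations fit its wording equally well.
- A reader might infer that the regression adjusts for on-study BMI, diet and activity. These variables are re-measured, but they are also collected at baseline, and adjusting for baseline values is sound. The stated purpose of re-measuring diet and activity is to follow their changes over time. Age and gender cannot be altered by allocation at all.

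A condensed article may leave both details to the full plan, so its silence is not an error.

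It is also fair to say that a split made only within the flaxseed arm cannot re-sort patients by arm, and that the article gives no expected shift for the lipids, metabolites or vascular regulators. The results in step 2 therefore apply only to a split or correlation that ignores arm, and to markers that the food moves. The loss of information and the non-randomised nature of the groups apply in either case.

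Finally, a regression with arm in the model still conditions on something measured after randomisation. That is correct: it removes the between-arm artefact but leaves confounding within arms.

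**Conclusion.** The point holds for the dichotomised marker-change analysis, which the article states. The groups it forms are not randomised subgroups, and a median split of a normal marker costs about 36% of the information (80 completers acting like about 51). If arm is ignored, allocation alone can produce a significant association, with a frequency that depends on the unknown marker shift as tabulated above. These rates assume a 0.7 SD effect on blood pressure, no within-arm link and 40 completers per arm. The 64% figure assumes normality and a median cut, and the article names no cut-point.

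For the correlations and the regression covariates, the article leaves the handling open. They call for a clarifying sentence and are not mistakes in the plan. The randomised comparison of blood pressure in the mixed model is untouched. What is exposed is the interpretation of the mechanism aim, so this is a worthwhile improvement to secondary analyses and not a threat to the trial's main result.

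**What to change.** - Drop the dichotomised marker-change subgroups.
- Regress change in blood pressure on marker change as a continuous variable, with arm and baseline blood pressure in the model.
- Compute the marker correlations in the same arm-adjusted (partial) form.
- Label these analyses exploratory, and say that an arm-adjusted association does not establish mechanism. If the fourth aim is to be claimed, specify a mediation analysis and its assumptions.
- State that the optional regression for the flaxseed effect uses baseline values of BMI, diet and activity alongside age and gender.

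The cost is a few sentences in the analysis section. No extra participants, visits or measurements are needed.
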